# Therapist-supported online cognitive therapy for post-traumatic stress disorder (PTSD) in young people: protocol for an early-stage, parallel-group, randomised controlled study (OPTYC trial)

**DOI:** 10.1136/bmjopen-2021-054852

**Published:** 2022-03-21

**Keywords:** mental health, child & adolescent psychiatry, anxiety disorders

## Abstract

**Introduction:**

Post-traumatic stress disorder (PTSD) is a disabling psychiatric condition that affects a significant minority of young people exposed to traumatic events. Effective face-to-face psychological treatments for PTSD exist. However, most young people with PTSD do not receive evidence-based treatment. Remotely delivered digital interventions have potential to significantly improve treatment accessibility. Digital interventions have been successfully employed for young people with depression and anxiety, and for adults with PTSD. However, digital interventions to treat PTSD in young people have not been evaluated. The Online PTSD Treatment for Young People & Carers (OPTYC) trial will evaluate the feasibility, acceptability and initial indications of clinical efficacy of a novel internet-delivered Cognitive Therapy for treatment of PTSD in young people (iCT-PTSD-YP).

**Methods and analysis:**

This protocol describes a two-arm, parallel-groups, single-blind (outcome assessor), early-stage randomised controlled trial, comparing iCT-PTSD-YP with a waiting list (WL) comparator. N=34 adolescents (12–17 years old), whose primary problem is PTSD after exposure to a single traumatic event, will be recruited from 14 NHS Child and Adolescent Mental Health Services in London and southeast England, from secondary schools and primary care in the same region, or via self-referral from anywhere in the UK using the study website. Individual patient-level randomisation will allocate participants in a 1:1 ratio, randomised using minimisation according to sex and baseline symptom severity. The primary study outcomes are data on feasibility and acceptability, including recruitment, adherence, retention and adverse events (AEs). The primary clinical outcome is PTSD diagnosis 16 weeks post-randomisation. Secondary clinical outcomes include continuous measures of PTSD, anxiety and depression symptoms. Regression analyses will provide preliminary estimates of the effect of iCT-PTSD-YP on PTSD diagnosis, symptoms of PTSD, anxiety and depression relative to WL. Process-outcome evaluation will consider which mechanisms mediate recovery. Qualitative interviews with young people, families and therapists will evaluate acceptability.

**Ethics and dissemination:**

The study was approved by a UK Health Research Authority Research Ethics Committee (19/LO/1354). For participants aged under 16, informed consent will be provided by carers and the young person will be asked for their assent; participants aged 16 years or older can provide informed consent without their parent or caregiver’s involvement. Findings will be disseminated broadly to participants, healthcare professionals, the public and other relevant groups. Study findings will be published in peer-reviewed journals.

**Trial registration number:**

ISRCTN16876240.

Strengths and limitations of this studyAn early-stage trial to gather data on feasibility, acceptability and initial indications of clinical efficacy of internet-delivered Cognitive Therapy for post-traumatic stress disorder in young people (iCT-PTSD-YP).Young people were extensively involved in designing the phone application and website.CT-PTSD is theory-based and has demonstrated efficacy when delivered face-to-face and iCT-PTSD is effective in adults.This trial can be delivered entirely remotely.This early stage randomised controlled trial is not powered to detect between group effects.

## Introduction

### Background and rationale

Trauma exposure and post-traumatic stress disorder (PTSD) are both prevalent among youth under 18 years old. Between 15%–82% of youth are exposed to traumas, and between 3%–8% of youth will develop PTSD by the age of 18 years,^1–3^ representing a significant level of morbidity for health services. For affected individuals, PTSD is highly distressing, causes marked impairments in functioning and may run a chronic course for years or decades if left untreated.^4 5^

Effective treatments for PTSD exist. Recent reviews of psychological treatments for PTSD in youth find that various forms of trauma‐focused cognitive behavioural therapy (TF‐CBT) show consistently large effects in reducing PTSD symptoms and associated comorbidities.^6 7^ Cognitive therapy for PTSD (CT-PTSD) is a form of TF-CBT developed by our group^8 9^ recommended as a first-line intervention in national and international practice guidelines.^10^ The treatment is theory-based, manualised and delivered over 10–12 individual sessions. Two published randomised controlled trials (RCTs)^11 12^ find that CT-PTSD is acceptable to young people (8–18 years old), and efficacious.^13^

However, most young people under 18 years old with PTSD do not receive an effective, evidence-based treatment. The gap between community prevalence of psychiatric disorders and treatment provision for young people is well-known and longstanding.^14^ In a recent population based British study, only 40% of young people with PTSD sought help from general practitioners (GPs) or mental health practitioners and only 20% had accessed specialist mental health services in the past year.^15^ Limited access to treatment may be due to multiple interacting factors including under-capacity and long waiting times for assessment and treatment in specialist Child and Adolescent Mental Health Services,^16^ and the burden and inconvenience to young people and families in attending face-to-face appointments in a clinic.

Remote delivery of psychological therapy via the internet has enormous potential to address some of these barriers, and to increase accessibility of treatment.^17^ Young people have enthusiastically endorsed the potential for digital health interventions.^18^ For disorders other than PTSD, digital health interventions are known to be acceptable to young people and clinically helpful. For example, computerised cognitive behavioural therapy (C-CBT) for depression demonstrates clear clinical benefit for young people^19 20^ and is now recommended by National Institute for Health and Care Excellence.^21^ Lessons have been learnt about the development of digital mental health interventions including the need for co-design with young people,^22^ and the active engagement of young people in therapy facilitated by continued therapist support during treatment.^19^

Development of remotely delivered therapy for treatment of PTSD in young people lags behind that for other disorders. Jaycox and colleagues^23^ report encouraging preliminary outcomes for a self-help web-based tool to augment and enhance usual school support services for trauma-exposed youth (7th – 12th grade, mean age 15 years). Kassam-Adams and colleagues^24^ showed that a digital intervention for preventing PTSD symptoms in injured children (8–12 years old) was feasible and clinically promising. Ruggiero and colleagues^25^ found that use of a web-based psychoeducation intervention for disaster-affected adolescents (mean age 14.5 years) was associated with improvements in PTSD symptoms. However, to our knowledge, no studies have yet reported on the development or evaluation of internet-delivered TF-CBT for treatment of PTSD in children and young people. This is surprising because face-to-face TF-CBT is well established as an effective treatment for PTSD in youth, and work with adults shows that PTSD is a disorder which is treatable via the internet.^26^

In this project we aim to address this clear gap. We have co-designed with adolescents an internet version of CT-PTSD, to be delivered via smartphone application and website, with remote therapist support. Our longer-term intention is to determine whether this approach will help to reduce the treatment gap for young people with PTSD by making an efficacious therapy more widely available. Our aim in the current early-stage trial is to gather preliminary data on feasibility, acceptability and initial signal of clinical effects of internet-delivered cognitive therapy for treatment of PTSD in young people (iCT-PTSD-YP), relative to a waiting list (WL) condition. Data gathered in the current trial will be used to inform the design and size of a future scaled-up trial. All items from the WHO Trial Registration data set are detailed in online supplemental appendix 1.

10.1136/bmjopen-2021-054852.supp1Supplementary data

### Objectives

The primary objective is to provide data on feasibility, acceptability, compliance, retention and delivery of iCT-PTSD-YP. The secondary objective is to provide initial estimates of the effect of iCT-PTSD-YP on symptoms of PTSD, anxiety and depression relative to a WL condition.

## Methods and analysis

### Trial design

This study is a two-arm, parallel groups, single-blind (outcome assessor), early stage RCT, comparing iCT-PTSD-YP with a WL comparator. Individual patient-level randomisation will allocate participants in a 1:1 ratio, randomised using minimisation according to sex and baseline symptom severity.

### Patient and public involvement

Members of the NIHR Maudsley Biomedical Research Centre (BRC) Young Person’s Mental Health Advisory Group (YPMHAG; 16–25 year-olds with lived experience of using mental health services) were consulted before grant submission: they provided verbal and written feedback on the research ideas. Young people (N=33, aged 12–17 years old) were consulted at an early stage about the design of the application via a series of four focus groups held in four different schools. Young people receiving face-to-face CT-PTSD provided feedback on initial prototypes of the application. A young person with lived experience of using mental health services is a member of the Trial Steering Committee (TSC). We will consult the YPMHAG and the TSC about our dissemination strategy.

### Study setting

The trial will be carried out in the UK. Trial randomisation will be carried out by King’s College London Clinical Trials Unit (CTU). Trial therapists will be based at King’s College London and the University of East Anglia. Referrals will be sought from 14 NHS Child and Adolescent Mental Health Services (CAMHS) in London and southeast England, all of which are registered as study sites. Referrals will also be sought from secondary schools and primary care in the same region. We will offer to carry out screening surveys in schools to identify potentially eligible young people (12–17 years old). Self-referral from anywhere in the UK is also possible via the study website.

### Eligibility criteria

Young people are eligible to be included if: they are aged 12–17 years old; their main presenting problem is PTSD and there is a not a comorbid problem that would preclude treatment of PTSD; PTSD symptoms relate to a single trauma; they speak English to a level that allows therapy without the need for an interpreter, and they read English to a level that allows independent use of iCT; they have access to a smartphone and a larger device (laptop, desktop computer, tablet) with internet access, and they have access to a safe and confidential space in which to engage in iCT. Young people are excluded if they have: brain damage; intellectual disability; pervasive developmental disorder or neurodevelopmental disorder, as assessed by clinical interview with parents/carers; other psychiatric diagnosis that requires treatment before PTSD, determined by clinical interview and questionnaires; moderate-to-high risk to self; ongoing trauma-related threat; have started treatment with psychotropic medication, or changed medication, within the last 2 months; or are currently receiving another psychological treatment, as assessed in clinical interview; or previously received TF-CBT in relation to the same traumatic event that they are currently seeking treatment for.

Parents or carers are eligible to be included if they: are the parent or carer of a young person who meets all of the inclusion criteria and none of the exclusion criteria above; speak English to a level that allows participation in therapy without the need for an interpreter, and read English to a level that allows independent use of iCT; and have access to a smartphone and/or larger device with internet access.

### Interventions

#### iCT-PTSD-YP

iCT-PTSD-YP comprises therapist-supported online delivery of all components from our published manual of face-to-face CT-PTSD for young people.^27^ Treatment aims to change problematic appraisals, update trauma memories and change unhelpful coping responses. Treatment components are delivered in modules. There are 10 core modules for all young people (Psychoeducation about PTSD, Reclaiming life, Understanding PTSD, Developing a trauma narrative, Identifying hotspots, Updating the narrative, Working with triggers, Overcoming sense of danger, Visiting the site virtually and/or in person, Developing a blueprint) that are released to the young person sequentially by the therapist, and 11 optional modules which are released according to individual need (Relaxation, Sleep, Working with images, Working with physical difference, Anger, Grief, Shame, Guilt, Self-criticism, Rumination and Panic). Modules were co-designed with input from young people and built on the content of the modules developed for iCT-PTSD for adults.^28 29^ Modules are interactive (prompting for user action to progress through the application and requesting user text input and questionnaire responses) and include text, illustrations, audio case examples, animations and videos. Modules are intended for independent self-study by young people. Therapists can log onto the site to view young people’s progress including their text input and questionnaire responses. Young people and therapists can message each other via the application. Parents and carers are provided a separate log on to the carer version of the application. The carer version comprises eight modules, and the emphasis is on providing information to carers about therapy, including advice about how carers can help in young people’s recovery. Carers do not have access to any information that their child inputs to the application. Modules are delivered via a progressive web application on a smartphone or computer, hosted on a secure server. The application is not publicly available currently. For trial participants, an individual account requiring two-factor authentication log-in is created for the young person and their carer.

Therapists will be clinical psychologists or CBT therapists who have received training in face- to-face CT-PTSD, and in use of the iCT-PTSD-YP application. Therapists will have contact with young people and carers via phone or videoconferencing at least once a week for the duration of therapy. Therapists release modules according to the young person’s individual formulation, remind and encourage young people to log on to the application and provide support in using the application and implementing the treatment components. Weekly clinical supervision will be provided by a consultant clinical psychologist from the trial team.

Therapy is delivered over 12 weeks. Post-treatment assessment is carried out 1 month after the end of treatment (ie, at 16 weeks after randomisation).

#### WL

Young people will be placed on a WL and re-assessed 16 weeks after randomisation. Young people who require treatment at the end of the waiting period will be offered immediate iCT-PTSD-YP. WL control arms are commonly used in PTSD treatment trials^6^ because natural recovery from PTSD can be substantial.^30^ Use of a WL condition ensures that the effect of treatment is not overestimated, and shows whether treatment is impeding the rate of natural recovery.

#### Withdrawals

Participants will be withdrawn from treatment if: a current illness prevents further treatment; there is a change in the participant’s condition or circumstances that in the clinician’s opinion justifies the discontinuation of treatment; or the participant withdraws consent for treatment. Participants who discontinue treatment for the above reasons will be invited to provide follow-up data and will remain in the trial for the purposes of data analysis. If the participant no longer wishes to be followed up to provide research data, the participant will be withdrawn entirely from the trial. The different types of withdrawal will be captured and reported.

### Outcomes

The schedule for assessments is presented in table 1.

**Table 1 T1:** Study schedule

Measure	Study period					
	Screen 0–1 week	Pre 0 weeks	Weekly (*iCT only*)	Mid 0+6 weeks	Post 0+16 weeks	Follow-up 0+38 weeks (*iCT only*)
Enrolment						
Eligibility screen	x					
Provide study information	*x*					
Gain informed consent		*x*				
Online assessment						
Dawba		*x*				
Interview						
Demographic interview						
CAPS-CA-5		*x*			*x*	
CGAS		*x*			*x*	
*Adolescent questionnaires*						
CPSS-5		*x*			*x*	*x*
CRIES-8		*x*	*x*	*x*	*x*	*x*
RCADS-C		*x*			*x*	*x*
CPTCI		*x*		*x*	*x*	*x*
TMQQ		*x*		*x*	*x*	*x*
Rumination items		*x*		*x*	*x*	*x*
CHU-9D		*x*			*x*	*x*
Adverse events				*x*	*x*	*x*
Carer questionnaires						
SDQ-P		*x*			*x*	*x*
RCADS-P		*x*			*x*	*x*
CA-SUS		*x*			*x*	*x*
Adverse events				*x*	*x*	*x*
Qualitative interviews						
Adolescents					*x*	
Carers					*x*	
Therapists					*x*	

CAPS-CA-5, Clinician Administered PTSD Scale for DSM-5: Child and Adolescent version; CA-SUS, Child and Adolescent Service Use Schedule; CGAS, Children’s Global Assessment Scale; CHU-9D, Child Health Utility Index 9D; CPSS-5, Child PTSD Symptom Scale for DSM-5; CPTCI, Child Post Traumatic Cognitions Inventory; CRIES-8, Children’s Revised Impact of Event Scale, 8-item version; DSM-5, Diagnostic and Statistical Manual of Mental Disorders; iCT, internet-delivered cognitive therapy; PTSD, post-traumatic stress disorder; RCADS-C, Revised Children’s Anxiety and Depression Scale—child version; RCADS-P, RCADS—parent version; SDQ-P, Strength and Difficulties Questionnaire—parent version; TMQQ, Trauma Memory Quality Questionnaire.

The primary outcomes for the study are data on feasibility, adherence and acceptability, which will be reported using the metrics specified below.

#### Feasibility outcomes

We will report: (1) the number of young people referred to the trial in total and according to referral route; (2) the number of young people screened in schools, and the proportion of those who proceed to a phone call with the family; (3) the number and proportion of young people in schools scoring above cut-off on a validated screening questionnaire (CRIES-8, see below) relative to the number of young people screened in schools; (4) the number and proportion of young people in schools who score above cut-off on the screening questionnaire but decline further participation with the trial relative to those scoring above cut-off); (5) the number and proportion of young people in schools who score above cut-off on the screening and consent to further assessment but are deemed ineligible at baseline assessment relative to those deemed eligible at baseline assessment; (6) the number of assessment appointments offered to participants; (7) the number and proportion of assessment appointments attended by participants, relative to the number of appointments offered, reported by referral source; (8) reasons for not attending assessment appointments, reported by referral source; (9) the number and proportion of young people who at baseline assessment consent to participate in the trial, relative to the number who attend assessment, with reasons for not consenting if known; (10) the number and proportion of young people eligible for the trial after baseline assessment, relative to the number of baseline assessments completed; (11) the number and proportion of young people who are randomised, and the proportion of consented young people who are randomised relative to the number who consented; (12) reasons for withdrawing from the trial if known; and (13) the number retained in study at 16 weeks (post-treatment) and at 38 weeks (follow-up), and the proportions of those who start treatment who are retained.

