### Recruitment

Participants will be recruited via three routes (see figure 1): (1) from school screening; (2) from NHS CAMHS teams; and (3) from primary care (GP or school referral) or self-referral. For all referral routes, consent will be sought before assessment, and eligibility will be determined by the clinical assessment.

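### Feasibility item 5, a primary metric, reports an odds under the label of a proportion; the consent that item 9 counts also needs to be stated

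*Protocol article*

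**What the plan says.** The Outcomes section fixes the status of these metrics: "The primary outcomes for the study are data on feasibility, adherence and acceptability". The numbered list under Feasibility outcomes then defines each one. Four items matter here.

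- Item 5 begins "5) the number and proportion of young people in schools who score above cut-off on the screening and consent to further assessment" and limits this to those who "are deemed ineligible at baseline assessment relative to those deemed eligible at baseline assessment".
- Item 9 concerns those "who at baseline assessment consent to participate in the trial, relative to the number who attend assessment", "with reasons for not consenting if known".
- Item 10 reports those "eligible for the trial after baseline assessment, relative to the number of baseline assessments completed".
- Item 11 includes "the proportion of consented young people who are randomised relative to the number who consented".

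On the timing of consent, the Recruitment section says: "For all referral routes, consent will be sought before assessment, and eligibility will be determined by the clinical assessment". Table 1 marks informed consent in the Pre (week 0) column, together with the baseline measures.

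**The concern.** Item 5 is called a proportion, but its numerator (the ineligible) is not part of its denominator (the eligible). A reader who sees the reported percentage will take it as the share of assessed school-route young people lost to ineligibility, and it is not that. The error grows with the share ineligible, and beyond one half the figure passes 100%.

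What is at stake is a primary feasibility figure. The article says in its introduction and discussion that the data will inform the design and size of a future trial. The yield from school screening bears directly on how many pupils such a trial would need to screen.

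A lesser doubt attaches to item 9. If everyone who attends assessment has already given trial consent, the ratio of consenters to attendees carries no information about uptake.

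**Working it through.** **Inputs.** The definitions of items 5, 9, 10 and 11 come from Feasibility outcomes, and the consent timing from Recruitment and Table 1. The article states no count, target or threshold for item 5 or item 9, so there is no figure of its own to reproduce. All values of p, all counts and all uptake rates below are assumptions for illustration.

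**Item 5.** Let I be the ineligible and E the eligible among school-route young people who completed baseline assessment, and let p = I/(I + E).

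- As written: I/E = p/(1-p).
- As labelled: I/(I + E) = p.

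| Share ineligible, p (assumed) | Item 5 as written, p/(1-p) |
|---|---|
| 20% | 0.20/0.80 = 25% |
| 40% | 0.40/0.60 = 67% |
| 50% | 0.50/0.50 = 100% |
| 60% | 0.60/0.40 = 150% |
| 80% | 0.80/0.20 = 400% |

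The same in counts: 10 ineligible and 20 eligible give 10/20 = 50% as written, against 10/30 = 33%. With 30 ineligible and 10 eligible, the item gives 30/10 = 300%, against 30/40 = 75%.

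**Item 5 beside item 10.** Item 10 is a true proportion, eligible over assessments completed. Suppose p = 40% on every route. Item 10 would read 60% eligible and item 5 would read 67% ineligible. The two add to 127%, where complementary shares would add to 100%. Item 5 also leaves open whether its eligible group is limited to the school route.

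**Item 9.** The result depends on what the consent in the Recruitment section is.

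1. It is trial consent, obtained before a person counts as attending. Every attendee has then consented, and item 9 = 100%. Assumed uptakes of 60%, 80% or 90% among those invited all give 100%.
2. It is trial consent, taken at the start of the attended appointment. Refusers are in the denominator, and the same assumed uptakes give 60%, 80% and 90%.
3. It is consent to be assessed only, with trial consent asked separately at the assessment. Item 9 is again an ordinary proportion of attendees.

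**Item 11** shares this dependence. If trial consent comes before eligibility is known, randomised over consented mixes ineligibility with later loss. If it comes after, it does not.

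**The case against.** On item 5, the case for leaving it is that nothing is lost. The number of ineligible young people is reported alongside, and the intended share follows from the ratio r as r/(1 + r): 0.667/1.667 = 40%, and 1.5/2.5 = 60%. Item 10 already gives a correct eligibility proportion across all routes. It covers a wider population than item 5, so the two would not match exactly even with item 5 corrected. No progression rule depends on either item, and the analysis is descriptive. All of this is true and limits the harm. It does not make the definition right: a reader should not have to convert a primary outcome back into what its label says.

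On item 9, a reader might infer that the consent rate is calculated among people who have already consented, so that its denominator is plainly wrong. The article does not support that. Item 9 itself places consent at the baseline assessment and provides for reasons for refusal, so it expects refusers among attendees. Table 1 puts consent in the same column as the baseline measures. Item 5 mentions consent to further assessment, which may be a separate step from consent to the trial. Consent sought before assessment can mean at the start of the attended appointment. What stands is an unresolved question of which consent and when.

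A reader might also infer that refusals outside schools go uncounted. That too is overstated. Item 1 counts referrals by route, item 6 counts appointments offered, items 7 and 8 give attendance and reasons for non-attendance by referral source, and item 9 is not limited to schools. What the other routes lack is only a separate count of decliners such as item 4 gives for schools.

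**Conclusion.** Item 5 is wrong as written. It yields an odds where it promises a proportion, overstates the share ineligible whenever anyone is ineligible, passes 100% once more than half are ineligible, and is not on the same scale as item 10. The algebra needs no assumption; the size does, because the article gives no counts (40% would be reported as 67%, and 60% as 150%). The consequence is a misleading primary feasibility figure, recoverable from the counts. It does not threaten the trial or its clinical analyses.

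Item 9 is a matter for clarification. It is uninformative only under the first of the three readings set out above, and the article does not establish that reading.

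**What to change.** **Item 5.** Define the denominator as all school-route young people who scored above cut-off, consented to assessment and completed the baseline assessment, and report the ineligible as a share of these. State that both counts are limited to the school route.

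**Items 9 and 11.** Reconcile the Recruitment section with item 9 by stating whether the consent counted is consent to assessment or to the trial, and whether it is taken before or at the attended appointment. If trial consent is obtained before attendance, use the number invited as the item 9 denominator, reported by referral route, or state that invitation counts were not kept. If trial consent is asked at the appointment, the item 9 denominator can stay, and the Recruitment sentence should say so. Read item 11 in line with the answer.

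**Cost.** Wording only. Recruitment has closed, but these are reporting definitions, and the item 5 correction uses counts that the existing item already requires. Only invitation counts by route might prove unavailable, and then a statement to that effect is enough.
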